## Data safety and privacy

All data will be handled according to the Medical Confidentiality Rules and German Federal Data Security Law. Patient names and other confidential information will be coded to disable the tracking of individual patients. Informed consent and questionnaires will be mailed separately.

## Ethics

The trial is planned and will be conducted in accordance to the medical professional codex and the Helsinki Declaration of 1996 as well as the German Federal Data Security Law. The study protocol was approved by the ethics committee of the University of Göttingen (ethic committee University Medical Centre Göttingen, protocol number 2/9/10). Patients receive written and oral information about the flow of the study, its aims, potential benefits and risks prior to their consent and participation in the trial. If they agree to participate, they sign the informed consent sheet. Patients are informed that they may withdraw from the study at any time without disclosing reasons and without negative consequences for their medical care.

## Statistical analysis

We expect a total number of 22 practices which will be randomized to the two intervention arms. Assuming an intra-cluster correlation coefficient of 0.05 [22], 15 patients per practice (i.e. 22 × 15 = 330 patients in total) will give a power of at least 80% at a two-sided significance level of 5% if the standardized intervention effect is at least 0.41, which is considered a medium effect size [23]. Accounting for patient dropout, we plan to recruit a total of 360 patients, i.e. about 16 patients per practice. We do not expect any practices to drop out.

Baseline and follow-up data will be presented using standard descriptive statistics and graphs. Allowing for correlation the primary endpoint will be modelled in a mixed linear model with intervention, baseline OAT knowledge and, if imbalances between the groups occur, possibly other factors as fixed effects and a practice effect as a random cluster effect. Main interest is in testing the null hypothesis of no intervention effect. The p-value for this test will be reported alongside a 95% confidence interval for the intervention effect. Standard diagnostics will be applied to check for model fit. If model assumptions are not met, non-parametric rank-based procedures will be considered. The mixed linear model described above is to some extent robust to missing data. If the proportion of missing data is much higher than expected, alternatives will be explored [24]. Percentage time in range will be calculated according to Rosendaal's equation [25].

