### Patients

In order to minimize sub-sampling bias, all patients with OAT will be identified at the beginning of the trial by searching the GPs' electronic medical records for the laboratory billing code "32015" for INR measurement. The inclusion criteria are age (> 18 years), OAT and willingness to participate in the trial. For dependent patients, both they and their caregivers (e.g. care giving relatives) must be willing to participate. Exclusion criteria include the inability to give informed consent and/or the lack of a caregiver willing to participate in the study. Also, nursing home residents, patients only seen in cross coverage, or patients with an insufficient command of the German language will be excluded. Lastly, patients managing anticoagulation with self-monitoring (PSM) will also be excluded.

During their next visit for INR-measurement age and gender of all eligible patients will be recorded. Patients will receive an information leaflet regarding the purpose and content of the study. Patients willing to participate will fill in a consent form. If there are further questions, patients, caregivers and/or practice nurses are encouraged to contact the study doctors.

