## Randomization

The randomization of the GPs to the intervention or control group will be conducted externally by Department of Medical Statistics, University Medical Centre Göttingen using a computer routine (allocation ratio 1:1).

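### The stated 80% power at an effect of 0.41 ignores the small number of practices: on about 20 degrees of freedom the same inputs give about 78% before any credit for baseline adjustment

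*Protocol article*

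**What the plan says.** The power statement is in the protocol article, section Statistical analysis. The number of clusters comes first: "We expect a total number of 22 practices which will be randomized to the two intervention arms". The other inputs follow: "Assuming an intra-cluster correlation coefficient of 0.05" and "15 patients per practice (i.e. 22 × 15 = 330 patients in total". From these the article concludes that the design "will give a power of at least 80% at a two-sided significance level of 5% if the standardized intervention effect is at least 0.41". A margin is added for individual losses, "Accounting for patient dropout, we plan to recruit a total of 360 patients, i.e. about 16 patients per practice", and none for practices: "We do not expect any practices to drop out".

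The section Randomization confirms that practices are the randomized unit, "using a computer routine (allocation ratio 1:1". The primary model is a linear mixed model with intervention and baseline knowledge as fixed effects and practice as a random effect. The power statement names no reference distribution and no allowance for variation in practice size, and it does not say whether a gain from baseline adjustment is counted. On practice size, the section Patients says only that "all patients with OAT will be identified at the beginning of the trial"; it gives no quota per practice.

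**The concern.** When practices are randomized, the information on the intervention effect comes from differences between practices. With 11 practices per arm, the variance of that contrast is estimated on about 22 − 2 = 20 degrees of freedom, however many patients each practice contributes. The usual design-effect formula inflates the variance for clustering but then treats the test as if that variance were known. With 22 clusters this costs several points of power. The margin in the stated figure is small, so the loss is enough to take it below the promised minimum of 80%.

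This is the article's only power claim for the primary outcome, and all its inputs are given. A reader would take 0.41 as the effect that the trial detects with at least 80% power.

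**Working it through.** **Inputs from the article.** 22 practices, 1:1, so 11 per arm; 15 analysed patients per practice, so 165 per arm; intra-cluster correlation 0.05; two-sided 5%; standardized effect 0.41 (SD = 1).

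**Step 1: reproduce the stated figure.**
- Design effect = 1 + (15 − 1) × 0.05 = 1.70.
- Effective size per arm = 165 / 1.70 = 97.06.
- Standard error = √(2 / 97.06) = 0.1435.
- Noncentrality = 0.41 / 0.1435 = 2.856.
- Normal approximation: Φ(2.856 − 1.960) = 81.5%; detectable effect at 80% power 0.402.
- A t test on 328 patient-level degrees of freedom (330 − 2) gives 81.3%. It also ignores the number of clusters.

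So the stated figure is the result of a standard large-sample calculation.

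**Step 2: use the cluster-level degrees of freedom.** The critical value of t on 20 degrees of freedom is 2.086. A noncentral t with noncentrality 2.856 gives 77.5% (77.3% on 19 degrees of freedom). For 80% the noncentrality must be 2.945, so the detectable effect is 2.945 × 0.1435 = 0.423. With 16 analysed patients in every practice, power is still 79.0%.

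**Step 3: unequal practice sizes.** The article gives no size distribution, so the coefficients of variation (CVs) are assumptions. A mixed model weights practices by their information. Its efficiency relative to equal sizes is about 1 − CV² × λ(1 − λ), with λ = 15 × 0.05 / (15 × 0.05 + 0.95) = 0.441 and λ(1 − λ) = 0.2465.
- CV 0.3: efficiency 0.978, noncentrality 2.856 × √0.978 = 2.824, power 76.6%, detectable effect 0.423 / √0.978 = 0.428.
- CV 0.5: efficiency 0.938, noncentrality 2.767, power 74.9%, detectable effect 0.436.
- CV 0.65: efficiency 0.896, noncentrality 2.703, power 73.0%, detectable effect 0.447.

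Averaging over simulated gamma-distributed sizes gives 76.5 to 76.7%, 74.8 to 75.1% and 73.0 to 73.6%, in agreement. The cruder design effect 1 + ((1 + CV²) × 15 − 1) × 0.05 gives 76.0%, 73.2% and 70.4%, which is too pessimistic for the planned model.

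**Step 4: baseline adjustment.** Assume that 0.41 is on the unadjusted SD scale and that baseline knowledge reduces the between-practice and within-practice variance in the same proportion, R². The R² that restores 80% on 20 degrees of freedom is 1 − efficiency × (2.856 / 2.945)² = 1 − efficiency × 0.940.
- Equal sizes: R² = 0.06, correlation about 0.25.
- CV 0.5: R² = 1 − 0.938 × 0.940 = 0.118, correlation about 0.34.

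With equal sizes, R² of 0.10 gives 81.7% and R² of 0.20 gives 85.9%.

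**The case against.** The strongest reply is that 77.5% is not the power of the planned test. The primary model adjusts for baseline knowledge, the questionnaire is given at baseline and again at six months, and a correlation of only about 0.25 would be enough to reach 80% with equal practices. This stands, and it limits the conclusion: the power of the planned analysis cannot be fixed at 78% and may exceed 80%. It does not rescue the sentence as written, because the power statement neither uses the adjustment nor gives a correlation. If 0.41 is already on the adjusted SD scale, no further credit remains.

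A second reply is that the design-effect method is standard and the figure reproduces. That is correct. A reader might infer an arithmetic slip; there is none. Nor does the stated figure depend on exactly equal practices, since the normal approximation still gives 80.0% at a CV of 0.3 even with the cruder design effect. What is missing is an allowance for the number of clusters.

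A third reply concerns the test itself. A reader might infer that its type I error is inflated: a z reference on 20 degrees of freedom would have a true level of 2 × P(t > 1.96) = 6.4%. The article does not say that a z reference will be used, and an article commonly leaves the degrees-of-freedom method to the full protocol or SAP. Inflation is therefore not established.

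Finally, a reader might count the absence of an allowance for lost practices as an error. It is an openly stated assumption, and any loss is hypothetical. For scale, losing two practices of equal size would give about 73%.

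**Conclusion.** The point holds in a limited form. The unqualified minimum of 80% at 0.41 follows from the stated inputs only if the small number of clusters is ignored. On about 20 degrees of freedom, with equal practices and no baseline credit, power is 77.5%, which is 2.5 points below the claim, and 80% is reached at 0.423 instead of 0.41. These two figures need only the article's own inputs and the cluster-level degrees of freedom.

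The figures for unequal sizes rest on assumed CVs. The break-even correlations rest on the variance assumption in the working. It would go too far to conclude that the trial is underpowered: the documents give neither the baseline correlation nor the spread of practice sizes, and a modest correlation would close the gap. The shortfall is small, but it affects the article's only power claim and is easy to correct.

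**What to change.** Choose one of two restatements of the power sentence:
- about 78% power at 0.41, or 80% power at about 0.42, on 20 degrees of freedom with equal practice sizes and without credit for baseline adjustment; or
- keep 80% at 0.41 and state the baseline to six-month correlation that supports it (at least about 0.25 with equal sizes, about 0.34 at a CV of 0.5), with its source.

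In either case give the assumed CV of practice size. Specify Kenward-Roger or Satterthwaite degrees of freedom for the intervention test, so that the analysis matches the restated power.

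The cost is one rewritten sentence, with a slightly less favourable figure under the first option, and one model option. No additional patients or practices are required.

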## Discussion

To our knowledge this will be the largest cluster-randomized controlled trial to evaluate the long-term effects of a complex patient education program about OAT in comparison to a patient information brochure only. An educational video has been used previously in a small American study (n = 22) [26]. So far, most studies only evaluated the short-term effects of education programs or assessed the acceptance of education programs for patients with OAT but not its effectiveness [17,19]. Moreover most studies were done with patients trained for self management (PSM).

Our trial will provide data about patient knowledge, the effect of education on time spent within therapeutic range and the rate of complications. Although we record complications in our study, we expect that the frequency will be too low to detect significant differences between the groups. If we can prove an increase of long-term knowledge of patients about OAT by a video-assisted education program, this program could be incorporated into routine OAT in primary care to increase patient safety.

Recruitment into this study is scheduled to the start in early 2011.

## Abbreviations

The following abbreviations have been used in the manuscript:

INR: international normalized ratio; GP: general practitioners; OAT: oral anticoagulation therapy; PSM: patient self-management.
